### Trial oversight

For the implementation of ferritin-guided donation intervals, the Sanquin Blood Bank has formed a Ferritin Steering Committee including senior clinical, laboratory, managerial and academic members who monitor the overall conduct of the implementation of ferritin-guided donation intervals. The Ferritin Steering Committee provides Sanquin’s Board of Directors and Sanquin’s Medical and Ethical Advisory Boards with advice regarding the implementation, including the timing and number of clusters for each implementation step. Additionally, the Ferritin Project Committee involves staff members responsible for practical aspects of the implementation, such as communication to donors, training of blood collection staff, laboratory testing and Information Technology. Finally, the FIND’EM Research Team, consisting of researchers authoring this paper, monitors the data collection and analyses for the study. Some overlap in members of the Ferritin Steering and Project Committees and the FIND’EM Research Team enables easy information exchange and smooth coordination of activities.

## Discussion

Currently, there is no international consensus on an appropriate policy for iron monitoring in whole blood donors. To our knowledge, this is the first randomised study to evaluate the effectiveness of ferritin-guided donation intervals on Hb and ferritin levels, low-Hb deferrals, return rates and health of donors.

The use of a stepped wedge cluster randomised trial approach allows to implement and simultaneously evaluate the policy. As data collection takes place at multiple time points during the implementation period, all blood collection centres contribute data under both the control and intervention condition. Furthermore, this design makes it possible to investigate the effects as if it was a randomised controlled trial by correcting for time and clustering of donors and blood collection centres. This design also introduces some challenges, including prolonged trial duration compared to a standard randomised controlled trial, time-varying confounding, instructing all parties involved, making sure each cluster is committed and performing the assigned policy, and communication with whole blood donors [14, 21]. Furthermore, the lack of blinding to the allocation for both participants and trial staff may introduce a risk of bias [22]. Recruitment bias for the questionnaire data is limited by inviting all eligible donors at the different measurement time points to participate. For other outcomes, all available information from donors who gave consent for their unusable remainder of the donation to be used for medical scientific research was used in the current study. Detection bias is expected to be minimal because outcome assessment does not include any judgement from the researchers [22]. For our sample size calculation, we considered multiple clustering effects that may be present in our study design. An individual autocorrelation coefficient will not affect our sample size as there are no repeated measurements from the same participants. As participants in the same cluster are more alike than participants in another cluster, we included an intraclass correlation coefficient of 0.10. Finally, it may be necessary to take into account a cluster autocorrelation coefficient. However, the cluster autocorrelation coefficient may be difficult to determine and the impact on the total sample size is probably limited [23]. Although the appropriate sample size calculation for stepped wedge designs is still subject of discussion, it is a potential limitation that we did not take into account a cluster autocorrelation coefficient in our sample size calculation. The setting of Sanquin as one organisation with multiple blood collection centres has some advantages in the execution of a stepped wedge cluster randomised trial compared to locally organised general practices or hospitals, for example. The blood collection centres are randomised to implementation steps and instructed to perform the assigned policy, with centralised organisation and monitoring. To our knowledge, this method has never been used in transfusion-related research. The effectiveness of the ferritin-guided donation interval policy on Hb and ferritin levels, Hb deferral rates, donor return rates and donor health likely has a delayed response, because (1) donors’ ferritin levels are only measured when they make a fifth donation and (2) the policy involves donation interval extension which delays follow-up. Delaying the implementation period of ferritin-guided donation intervals should therefore have minimal negative impact on the outcome of the study. Sanquin’s Ethical Advisory board approved the FIND’EM study protocol after the start of the implementation period and we were therefore not able to collect baseline questionnaire data in September 2017. Furthermore, this together with logistic constraints made it impossible to collect data at each implementation step. Therefore, we might have less detailed data on the effects of the new policy on the outcomes over time compared to a design with outcome measurements at each cross-over period. The secondary outcome donor health is measured at mid-implementation and after complete implementation. Investigating the effectiveness of the ferritin-guided donation intervals policy on donor health is limited to the use of questionnaire data collected at mid-implementation and after the implementation period. Data on ferritin levels is available at baseline, mid-implementation and after complete implementation of the policy.

Worldwide, increasing numbers of blood services consider implementing routine ferritin measurements in blood donors, though the effectiveness of ferritin-guided donation intervals has not yet been evaluated. Iron supplementation is an often-applied alternative intervention to limit iron deficiency in whole blood donors. Iron supplementation may increase iron stores in a shorter amount of time, thereby allowing blood donors to continue donating according to their regular donation interval [24]. Although some studies have evaluated the effect of oral iron supplementation on ferritin levels in blood donors, the recommended dosage and frequency of iron supplementation is unknown and the donors’ perception of iron supplementation should be further investigated. Overall, there is a general lack of evidence and consensus on the appropriate ferritin monitoring policy.

The FIND’EM study will provide ground-breaking evidence on the effectiveness of ferritin-guided donation intervals on Hb and ferritin levels, low-Hb deferral, donor return rates and donor health. This evidence will help blood services worldwide to improve donor iron management policies in order to protect and improve the health of donors.

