### Study population

Both new (i.e. a donor undergoing pre-donation screening) and repeat donors (i.e. a donor making a whole blood donation or attempt) are eligible to participate in this study. The intervention likely results in delayed effects. Ferritin levels of a donor visiting a blood collection centre where the intervention has been implemented will only be measured every fifth donation. Furthermore, the extension of donation intervals makes it necessary to allow the blood collection centres to be exposed to the intervention for a certain amount of time before donors return and the effectiveness of the new policy becomes observable. We therefore selected three measurement time points: (1) before implementation (i.e. baseline), (2) mid-implementation (when 55% of blood collection centres had implemented the policy) and (3) after complete implementation of ferritin-guided donation intervals. As Sanquin had already started the implementation of the ferritin-guided donation intervals in November 2017, before approval from the Ethical Advisory Board for the FIND’EM study, we were unable to collect questionnaire data from donors at baseline. However, baseline data on other outcomes (Hb and ferritin levels, low-Hb deferral and donor return) are measured after ethical approval in stored samples, and a large majority of the donors (99%) provide their consent to the routine request to ‘make the unusable remainder of my donation available for medical scientific research in general’ (Fig. 2). Whole blood donors who visit one of the 50 fixed blood collection centres during a pre-selected week at mid-implementation or after complete implementation are asked to participate by completing questionnaires. This makes the current study an open cohort design study with repeated cross-sectional measures and new samples at each measurement. Donors registering at the registration desk of one of the collection centres during one of these time points will receive a leaflet with information on why this study is performed, explaining that upon participation, the donor is asked to fill in a questionnaire and participation is voluntary, the leaflet contains contact details of the research team in case of any questions and a link to the study website with additional information and frequently asked questions. The donor is asked to read the study information while waiting for their health check. After the check, the donors will be asked whether they have read the study information. If the donor decides to participate, an informed consent form will be signed and the donor physician or nurse will sign the form as a representative of the researcher. Donors who decide not to participate are asked to write down the reason for non-participation.

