### Data collection

Pseudonymized data on age, sex, Hb levels and deferrals will be extracted from the donor database (eProgesa software application; MAK-SYSTEM) for all new and repeat whole blood donors who visit a fixed blood collection centre during a pre-selected week at one of the three measurement time points and gave consent for their information and left-over material to be used for research purposes. Furthermore, we will calculate donor return rates as the percentage of donors with a donation attempt within 6 months after the next allowed donation date. We will use stored plasma samples of new donors and repeat donors who made a donation attempt at one of the fixed blood collection centres during one of the pre-selected measurement time points to determine ferritin levels in intervention and control groups. Ferritin will be measured on the Architect i2000sr (Abbott Diagnostics) from donation samples collected in K3EDTA tubes (Greiner) and stored at − 30 °C. After storage, ferritin levels may be lower than those in fresh samples [16]. Within the FIND’EM study, we will compare ferritin levels of donors donating at centres where the ferritin-guided donation interval policy was implemented to ferritin levels of donors donating at centres where the policy was not implemented yet. For both groups, we will use samples that were stored for the same time period. Therefore, we expect similar decreases of ferritin levels as a result of storage in both groups, still allowing this comparison. For the validation of ferritin levels from stored samples of donors participating in the FIND’EM study, we will compare ferritin levels from stored samples with ferritin levels measured in fresh samples as part of the ferritin-guided donation interval policy.

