### Sample size calculations

Using data from the first clusters of blood collection centres that have implemented the ferritin-guided donation intervals, we found a mean increase in ferritin levels of 4 ng/mL (standard deviation (SD) 54 ng/mL) over a 6-month period. To detect a difference of 4 ng/mL, assuming a SD of 54 ng/mL, a two-sided significance level of 5%, a power of 80% and ignoring the correlated observations, a sample size of 5720 subjects is needed. We used the following formula to calculate the actual sample size:
$$ m=\frac{N}{1+\left(n-1\right)\left(1-\rho \right)} $$

where *m* = number of blood collection centres, *N* = sample size ignoring the correlated observations; *n* = average number of subjects within a blood collection centre and *ρ* = intraclass correlation coefficient. Assuming an average number of subject within each blood collection centre of 150 and an intraclass correlation coefficient of 0.1, we need 42 centres in total. With the fixed number of 50 blood collection centres (i.e. 7500 subjects), the power of the study is more than enough to detect the difference of 4 ng/mL. An individual autocorrelation coefficient is not included in our sample size calculation as we include repeated cross-sectional measures. With approximately 7500 donation attempts at fixed collection centres each week, we anticipate that we will be able to collect data on age, sex, Hb levels and deferrals and ferritin levels of approximately 7500 donors at baseline, mid-implementation and after implementation, thereby including more than sufficient data to reliably investigate the effectiveness of the ferritin-guided donation intervals. Furthermore, during data collection at mid-implementation, approximately 3500 donors filled in the questionnaires. We expect about the same response for the data collection after full implementation of the new policy.

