### Data analyses

Descriptive statistics will be provided for the donor population at baseline, mid-implementation and after full implementation. Linear mixed models (i.e., multilevel analysis) will be used to investigate differences in Hb and ferritin levels, low-Hb deferral, donor return rates and donor health between intervention and control groups using data collected at baseline, mid-implementation and after implementation. Two-level models with donors nested within blood collection clusters will be fitted, with a random intercept for cluster to adjust for the correlation between measurements of donors within the same cluster. All models include a binary variable indicating whether the observation was done before or after the start of the intervention and will be adjusted for the time point of implementation of the policy (fixed variable, time in months since the start of implementation period). Because of the nature of our outcome measures and because we include a new sample of donors at every measurement time point, we do not expect robust methods to be appropriate for sensitivity analyses. To investigate how the impact of ferritin-guided donation intervals develops over time, the latter will also be included as an effect modifier [14]. An intention-to-treat approach will be used and stratified analyses will be performed to investigate differences in the effectiveness of ferritin-guided donation intervals for male and female donors.

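### The article says no participant is measured twice, but its inclusion rule lets donors recur across the three weeks; the resulting error is small and conservative

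*Protocol article*

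**What the plan says.** The Discussion states: "An individual autocorrelation coefficient will not affect our sample size as there are no repeated measurements from the same participants". Two other sections rest on a related premise in softer words. Sample size calculations says: "An individual autocorrelation coefficient is not included in our sample size calculation as we include repeated cross-sectional measures". Data analyses gives two reasons for expecting robust methods to be unsuitable as sensitivity analyses; the second is "because we include a new sample of donors at every measurement time point".

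The rules on who enters the data are broader. Data collection takes database records "for all new and repeat whole blood donors who visit a fixed blood collection centre during a pre-selected week" at any of the three time points, subject to consent, and invites all attendees to the questionnaires at the two later time points. Study population makes new and repeat donors eligible and sums up the design thus: "This makes the current study an open cohort design study with repeated cross-sectional measures and new samples at each measurement". No section excludes a donor because of inclusion at an earlier time point. Setting caps donation at 5 times a year for men and 3 for women.

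The model in Data analyses has two levels, donors within clusters, with a random intercept for cluster only.

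**The concern.** Each measurement week is in effect a census of attendees at the same 50 centres, drawn from one pool of donors who are expected to come back. Study population explains that effects become visible only once donors return, and donor return is itself an outcome. Some donors will therefore be present in more than one selected week, and the statement in the Discussion is a property that the described design does not have.

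Ferritin, haemoglobin and questionnaire scores are correlated within a person. A model without a donor term treats two records from one donor as two donors of the same cluster, so its standard errors are not exactly right. The same premise is used to set aside the individual autocorrelation and, in part, to rule out robust methods. A reader who takes it at face value would not ask how many donors recur.

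**Working it through.** **1. The plan's own figures.** Inputs from Sample size calculations: difference 4 ng/mL, SD 54 ng/mL, two-sided 5%, power 80%.

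- Per arm: 2 × (1.960 + 0.842)² × 54² / 4² = 2861, so 5722 in total. The article says "a sample size of 5720 subjects is needed", which agrees within rounding.
- Centres, by the printed formula: 5720 / [1 + 149 × (1 − 0.1)] = 5720 / 135.1 = 42.3. The article says 42, which agrees. Whether that formula suits the design is a separate question and is not examined here.

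**2. Expected recurrence.** The article gives no overlap figure. Assume that a donor makes k attendances a year, evenly spread, with no drop-out. The chance of attending another given week is then k/52. The base is the article's figure of about 7500 attempts a week.

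| k per year | k/52 | of 7500 |
|---|---|---|
| 1 (assumed) | 1.9% | 144 |
| 2 (assumed) | 3.8% | 288 |
| 3 (women's cap) | 5.8% | 433 |
| 5 (men's cap) | 9.6% | 721 |

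The last row would need every attendee to be a man donating at the cap. With women in the sample the true share lies below it. Drop-out and the policy's deferrals would lower all rows, but not to zero.

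**3. Effect on the standard error.** Layout: 29 clusters and 3 time points, with all clusters control at the first and all intervention at the last. At the middle one, 16 have switched (8 + 4 + 4 from Study design; 16/29 = 55%, the share given in Study population). Donors per cluster and time point: 7500/29 = 258.6.

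The effect is essentially the difference between the 16 switched and 13 unswitched clusters in y₂ − (y₁ + y₃)/2, where y₁, y₂ and y₃ are a cluster's means at the three time points. Let v be the residual variance divided by the number of donors. Let f be the share of donors recurring between any two weeks in the same cluster, and r the within-donor correlation, so that the added covariance between time points is c = f·r·v. Then

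Var = v(1 + 1/4 + 1/4) + 0.5c − 2c = 1.5·v·(1 − f·r).

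The ratio of true to modelled standard error is therefore about √(1 − f·r). At ICC 0.1, v = 0.9 × 54² / 258.6 = 10.15, and the modelled SE is √[1.5 × 10.15 × (1/16 + 1/13)] = 1.46 ng/mL. A full generalised least squares calculation gives 1.45 at ICC 0.1 and 1.49 at ICC 0.01.

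| f | r = 0.5 | r = 0.9 |
|---|---|---|
| 1.9% | 0.995 | 0.991 |
| 3.8% | 0.990 | 0.983 |
| 5.8% | 0.986 | 0.974 |
| 9.6% | 0.976 | 0.956 |

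The table is for ICC 0.1. At ICC 0.01 the ratios run from 0.996 to 0.959, and linear instead of categorical time changes little. Power for 4 ng/mL in this layout rises by at most about 3.5 points (for example from 78.6% to 82.1% at f = 9.6%, r = 0.9).

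**4. Questionnaires.** There are two waves of about 3500 respondents. If response is independent across waves (assumed), overlap is 3500/7500 = 47% of the attendance overlap. At the 5.8% row this is 2.7% of respondents. Then √(1 − 0.027 × r) is 0.993 at r = 0.5 and 0.988 at r = 0.9, an effect of about 1%.

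**The case against.** The best defence is that this is one loosely worded sentence in a Discussion. Only that sentence literally denies repeat measurement. A repeated cross-sectional design with a new sample each time can mean a fresh draw, not different people, and the open-cohort label already allows recurrence. The numerical effect is slight, it does not inflate type I error, and handling of duplicate records is often left to an analysis plan that is not shown here.

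Much of this stands. Sample size calculations and Data analyses should not be read as making the same denial. They matter because their rationales lean on the premise. The reply on the unshown plan does not carry, because the objection is to a property that the article asserts and its own inclusion rule does not deliver.

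A reader might also infer stronger conclusions, which the document does not support:

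- **That the treatment estimate is biased because overlap differs by condition.** Longer intervals under the policy could change who recurs, but nothing in the article gives a size or direction, and overlap by itself does not bias the estimate.
- **That the sample size fails.** Recurrence makes the between-week contrasts slightly more precise, so 5720 is not undermined on this ground.
- **That within-person information is thrown away.** All records stay in the model. The article chose a comparison of policy across clusters, not a cohort analysis.

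Finally, a donor random effect is not entirely free. Most donors are seen once, so its variance is weakly identified, and a donor who moves between clusters breaks simple nesting.

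**Conclusion.** The statement that no participant is measured more than once is wrong as written. It conflicts with the inclusion rule and with the open-cohort description, and the cluster-only model treats recurring donors' records as if they came from different people. The expected overlap is about 2% to under 10% between any two weeks. The consequence is a modelled standard error for the overall effect that is roughly 0.5% to 4% too large: a small error on the conservative side.

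That donors recur is an inference from the stated donation frequencies. The sizes rest on assumptions that the article does not supply: 1 to 5 evenly spread attendances a year, no drop-out, recurrence within the same cluster, within-donor correlation of 0.5 to 0.9, and ICC between 0.01 and 0.1. The correction is still worthwhile, because the statement supports modelling decisions and can be checked with data that the trial already holds.

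**What to change.** 1. Correct the Discussion sentence to say that donors may be measured at more than one time point. Reword the reasons in Sample size calculations and Data analyses that lean on the same premise, including the reason given against robust methods.
2. Report the number of donors seen at two and at three time points, by condition.
3. Use the pseudonymised donor identifier (calculating return already requires linking a donor's visits) to add a donor random effect, crossed with cluster where donors change cluster.
4. Add a sensitivity analysis with one record per donor. For the binary outcomes, low-Hb deferral and return, this may serve alone if the donor variance cannot be estimated.

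The cost is a few sentences, one count table, slightly more analysis work and a weakly identified variance component. No new data are needed.

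### At the plan's own ICC of 0.1, the reassurance that the cluster autocorrelation matters little for the sample size holds only if that coefficient is very close to 1

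*Protocol article*

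**What the plan says.** The sample size section of the protocol article starts from a comparison of independent observations (4 ng/mL, SD 54 ng/mL, two-sided 5%, power 80%) and concludes that "a sample size of 5720 subjects is needed". It then allows for clustering: "Assuming an average number of subject within each blood collection centre of 150 and an intraclass correlation coefficient of 0.1, we need 42 centres". Because 50 centres are available, it describes the power for 4 ng/mL as comfortably sufficient. It expects about 7500 donors at each of the three measurement time points.

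The Discussion returns to clustering. It keeps the ICC: "As participants in the same cluster are more alike than participants in another cluster, we included an intraclass correlation coefficient of 0.10". On the CAC, it says that "the cluster autocorrelation coefficient may be difficult to determine and the impact on the total sample size is probably limited", citing a source. The next sentence calls leaving the CAC out a potential limitation. No CAC value appears anywhere. The Data analyses section fits a random intercept for cluster only, which amounts to a CAC of 1.

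**The concern.** The CAC is the correlation between a cluster's underlying means in two different waves, relative to the correlation within one wave. A value below 1 means that part of the between-cluster variance is new at each wave and does not cancel when a cluster is compared with itself over time. How much this costs depends on the ICC and on the number of donors per cluster and wave. With a small ICC or small cells, sampling error dominates and the CAC hardly matters. Here the ICC is set at 0.1 and the cells are large, so even a small wave-specific share can exceed the sampling error.

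A reader of the two sections would conclude that the trial is well powered for 4 ng/mL and that the acknowledged limitation is minor. If that is wrong, a ferritin result that is not significant could be taken as evidence of no effect, in a study meant to guide policymakers.

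**Working it through.** **Reproducing the plan's figures.** Independent samples: total N = 4(1.960 + 0.842)² × 54² / 4² = 5722, against 5720 stated. Printed formula: 5720 / (1 + 149 × 0.9) = 42.3, against 42 stated. Both reproduce. Neither step contains the waves, the rollout or a CAC. Whether the printed formula is appropriate is a separate question.

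**Inputs.**
- Difference 4, SD 54, ICC 0.1, two-sided 5%: sample size section.
- K = 29 randomised clusters: Study design.
- Three cross-sections with new donors at each: Study population.
- Exposure 0, 16 and 29 of 29 clusters: by steps 1, 2a and 2b, 8 + 4 + 4 = 16 clusters (55%, as stated for mid-implementation); all at the end.
- n = 7500 / 29 = about 259 donors per cluster and wave.
- CAC: assumed, 1 down to 0.8.

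**Formula.** Let a = ICC × SD² × CAC (variance shared across waves) and b = ICC × SD² × (1 − CAC) + (1 − ICC) × SD² / n (variance of a cell mean specific to the wave). With wave as a factor, exposure differs between clusters only in the middle wave, and the generalised least squares variance is

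Var = [b(b + 3a) / (b + 2a)] / [k(K − k) / K], with k = 16 and k(K − k)/K = 16 × 13 / 29 = 7.172.

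Power = Φ(4/SE − 1.96). Detectable difference at 80% power = 2.80 × SE.

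**CAC 1.** a = 291.6; b = 0.9 × 2916 / 258.6 = 10.15. Var = 10.15 × 884.9 / 593.3 / 7.172 = 2.11; SE 1.45; power 78.6%.

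**CAC 0.95.** a = 277.0; b = 14.58 + 10.15 = 24.73. Var = 24.73 × 855.8 / 578.8 / 7.172 = 5.10; SE 2.26; power 42.5%; variance ratio 5.10 / 2.11 = 2.42. The 5% wave-specific share (14.58) already exceeds the sampling variance (10.15).

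**Range of CAC at ICC 0.1.** The last column treats the 50 centres of 150 donors as the clusters, with 27 exposed at mid-implementation; 28 exposed changes power by less than half a point.

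| CAC | SE (29) | Variance ratio (29) | Power (29) | Detectable difference, ng/mL (29) | Power (50 × 150) |
|---|---|---|---|---|---|
| 1 | 1.45 | 1 | 79% | 4.1 | 79% |
| 0.99 | 1.65 | 1.3 | 68% | 4.6 | 73% |
| 0.98 | 1.82 | 1.6 | 59% | 5.1 | 67% |
| 0.95 | 2.26 | 2.4 | 43% | 6.3 | 54% |
| 0.9 | 2.83 | 3.8 | 29% | 7.9 | 40% |
| 0.8 | 3.70 | 6.5 | 19% | 10.4 | 27% |

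On the 50 × 150 layout the variance ratio at CAC 0.95 is 1.82.

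**What the ratio means.** It counts clusters of equal size: 80% power needs 31 clusters of 259 at CAC 1 and 73 at CAC 0.95. With unlimited donors in the 29 clusters at CAC 0.95, b falls only to 14.58, so Var = 14.58 × 845.6 / 568.6 / 7.172 = 3.02, SE 1.74, and power stops at about 63%.

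**Sensitivity to the model.** Linear time in months instead of wave effects (waves assumed at months 0, 15 and 26) gives 78.7% and 42.6% at CAC 1 and 0.95. If the correlation instead decays by 0.95 per wave, the ratio is 1.99 and power about 50%.

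**Sensitivity to the ICC.** With 29 clusters and CAC 0.95, the ratio is 1.67 at ICC 0.05, 1.25 at 0.02 and 1.12 at 0.01.

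**The case against.** The strongest defence is that the article is candid. It says probably, cites a source and lists the omission as a limitation. All of that stands, so there is no ground for saying that the omission was hidden. The cited source is not at hand, and what it shows in general cannot be judged here; the sentence is, however, applied to this trial, whose own figures can be checked.

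It is also fair that 0.95 is not the plan's value. A reader might infer from the table that the trial has 43% power, or that the sentence is simply false. The documents support neither, because they give no CAC. Nor do they support saying that the trial would miss a 4 ng/mL effect more often than not: with 29 clusters that needs a CAC of about 0.96 or lower (at 0.97 power is still 52.5%), and on the 50 × 150 layout power at 0.95 is still above one half.

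The 50 × 150 layout is the one used for sizing, and it is milder. The 29 clusters are nevertheless the units that were randomised and that carry the random intercept, so they are the natural basis. The conclusion is the same on both.

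Finally, the ICC of 0.1 is itself a planning assumption, and at about 0.01 the reassurance would be reasonable. The plan cannot, however, take 0.1 for sizing and rely on the behaviour of a much smaller ICC for this sentence.

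**Conclusion.** The point holds as a conditional one. At the plan's ICC of 0.1, the claim of limited impact is true only if the CAC is almost exactly 1: a CAC of 0.99 costs about 11 points of power with the 29 clusters (78.6% to 68.0%) and about 6 points with 50 × 150 (79.0% to 72.7%). Roughly 26 months separate the baseline of September 2017 from the final measurement at the end of November 2019, which makes a CAC of exactly 1 optimistic. The description of the power as ample is not met even at CAC 1, where it is about 79%.

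The ratio of 2.4 at CAC 0.95 should not be read as 2.4 times as many donors. It refers to clusters, and the trial already includes all 29 in the country.

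The figures rest on equal cluster sizes, a normal approximation, the SD and ICC of the sample size section, and assumed CAC values. The fault is a reassurance about a design property that the plan's own numbers do not support. Correcting the sample size formula or the analysis model would not remove it, because the loss of precision belongs to the design.

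**What to change.** In the Discussion, delete the half of the sentence that calls the impact on the sample size limited, and keep the acknowledgement of the limitation. In the sample size section, delete the statement that the power is ample. In their place, give the power and the detectable difference at 80% power over a range of CAC. For 29 clusters and ICC 0.1, the detectable difference is about 4.1, 4.6, 6.3 and 7.9 ng/mL at CAC 1, 0.99, 0.95 and 0.9. State that the CAC values are assumptions.

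When the ferritin data are in, estimate the ferritin ICC and CAC from the trial's three waves and report them beside the confidence interval for the policy effect. This needs a cluster-by-wave random effect, since a model with only a cluster intercept fixes the CAC at 1. Values estimated from Hb in the donor database may serve for the Hb outcome but should not stand in for ferritin, because the Introduction itself says that Hb does not reflect iron status.

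The cost is two reworded sentences, a short table, one variance-component estimate and a less favourable stated power. No extra donors, samples or clusters are needed.
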